### Randomization and Control of Cross-Contamination

Randomization will be concealed until after the initial screen and consents are obtained and an ID number is assigned to the subject. [name] will prepare sealed envelopes to implement randomization. Inside each envelope will be the subject's group assignment, determined using a random number generator, with randomization to be conducted in blocks by nursing home site and time to ensure equal assignments across the two groups at the completion of the study and approximately equal assignments throughout the study to control for unknown temporal effects. While randomization by site is an acceptable method for controlling cross-contamination of conditions, we will randomize by individual. The rationales for this decision are, first, nursing homes are unstable environments[51] and second, nursing home quality indicators can fluctuate from one six-month period to the next[52]. Changes in quality indicators may reflect changes in resident profiles and/or changes in quality of care, both of which could affect the results of our study if randomization occurred at the facility level. Randomization by subject will provide greater power than randomization by NH.

Cross-contamination is a significant threat because control and experimental interventionists have the potential to interact during the provision of mouth care. Training for CRB raters, control interventionists, and experimental interventionists will occur separately. There will be no cross-training. All team members will be blinded to the specific aims of the study. All team members (CRB raters, interventionists) will be blinded to their assignment to the control or experimental arms of the study. Interventionists will be instructed to provide mouth care in private bathrooms with only the CRB rater present, to avoid having interventionists inadvertently observe each other. CRB raters will be paired exclusively with their control interventionists or with their experimental interventionists, to avoid bias in rating.

The potential exists for the control interventionists to address CRBs in some way by virtue of their experiences or humanistic approaches to care. While this potential cannot be ethically eradicated, its possible influence on the results can be addressed by having the control and experimental interventionists complete a "Provision of Mouth Care Form" at the conclusion of each mouth care interface. The "Provision of Mouth Care Form" will have a group of forced-choice questions concerning the completion of mouth care. There will be one open-ended question that requires the interventionists to describe what, if any, activities he or she employed to provide mouth care. An open-ended question is preferable to listing strategies or techniques, because the listing of these items could unblind the interventionist and threaten the design of the study. The experimental interventionists would be trained to complete the form by writing specific threat reduction strategies taught to them during their training. The control interventionists would be instructed to simply complete the form. By having both control and experimental interventionists complete the same form, additional risks for cross-contamination are reduced.

The PD will conduct random observations of 10% of the mouth care sessions provided by the control interventionists. The PD will complete a checklist of care-resistant strategies taught to the experimental interventionists. If the control interventionist is successfully employing these strategies to reduce CRB, the control interventionist will be debriefed, compensated for unworked scheduled shifts, and removed from the study.

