***Time ***is an independent variable that will be incorporated into statistical models to determine the effect of the intervention on CRB and oral health status over specified temporal intervals and shifts (day and evening).

***Dosage ***and ***frequency ***of the intervention are independent variables that will be incorporated into statistical models to determine the effect of the intervention on CRB and oral health status, and to compare the efficacy of the intervention to standard mouth care. Dosage will be calculated by the observer, using a stopwatch to measure the duration of each mouth care session. Dosage is also used to calculate the rate of care-resistance using the RTC-r. Frequency will be measured by counting the number of times mouth care was completed; percentage of completed mouth care will be calculated for each NH subject by dividing the number of successful mouth care completions by 42 (twice daily mouth care for 3 weeks).

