### Statistical Analysis

Individual growth models using multilevel analysis will be used to estimate the efficacy of the intervention for reducing CRBs in persons with dementia, and to estimate the overall efficacy of the intervention using oral health outcomes. Multilevel models (also referred to as hierarchical linear models) will be used because repeated observations of participants are nested within nursing homes[48,64-68]. Multilevel models deal with the "unit of analysis" problem that face nested studies, that is the units of analysis are not independent, but instead the observations are clustered[48,66,69,70]. Because multiple observations are nested

within participants (i.e., repeated measures), individual growth models will be used. Among the advantages of using individual growth models are the ability to deal with an unequal number of measurement occasions among individuals and heterogeneity of variance[48,65,66,71].

Three-level multilevel models will be estimated for CRBs and oral health outcomes in which the first level is the date/time at which the behaviors or outcomes are observed; the second level is the participant; and the third level is the NH in which the participant resides. Explanatory variables to be included at the first level are dosage; frequency; time; and a dummy variable for baseline versus intervention. Explanatory variables to be included at the second level are a dummy variable for whether the participant is in the intervention group or control group; functional status; cognitive impairment; demographic data (gender, ethnicity, race, age, duration of stay in a nursing home); co-morbid conditions; and the use of psychoactive medications. Variables are discussed and defined above.

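### Allocation is blocked by nursing home and time, but the listed model has no time-block term; if outcomes differ between enrolment periods, the arm dummy's standard error is somewhat too large

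*Protocol article*

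**What the plan says.** All references are to the protocol article.

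- **Randomization and Control of Cross-Contamination.** Allocation is individual, with "randomization to be conducted in blocks by nursing home site and time to ensure equal assignments across the two groups". The purpose given for blocking on time is "approximately equal assignments throughout the study to control for unknown temporal effects". The same section remarks that "nursing home quality indicators can fluctuate from one six-month period to the next", but as a reason for randomising residents rather than facilities.
- **Statistical Analysis.** In the three-level model "the first level is the date/time at which the behaviors or outcomes are observed", the second level is the participant and the third is the nursing home. "Explanatory variables to be included at the first level are dosage; frequency; time; and a dummy variable for baseline versus intervention". The second level has "a dummy variable for whether the participant is in the intervention group or control group", with functional status, cognition, demographics, co-morbidity and psychoactive medication. Neither list contains a randomisation block or enrolment period.
- **Instruments and Measures.** Time is to show the effect of the intervention "over specified temporal intervals and shifts (day and evening".

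**The concern.** An analysis should normally carry the factors by which patients were allocated. Here the nursing home is carried and the time block is not. Blocking makes the arms balanced within each period, so differences between periods drop out of the true sampling error of the arm comparison. A model without a period term does not know this. It counts those differences as variation between residents and reports a standard error for the arm dummy that is too large.

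At stake is precision, not validity. The trial plans for only 60 completers, so an avoidable loss is worth a sentence if the remedy is cheap. The point concerns a model whose terms the article itself writes out, so it is not a request for detail that a condensed article may leave elsewhere.

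**Working it through.** **1. Does any listed term stand for the time block?** The level 2 list has none. At level 1 the only candidate is time. Its definition pairs temporal intervals with day and evening shift, which reads as position within a resident's 28 days (7 baseline, 21 intervention). The description of level 1 as date and time of observation is looser and does not rule out calendar time. The likelier reading is that enrolment period is not modelled.

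**2. The plan's own numbers used as settings** (Recruitment, Sample, Sample Size). 16 recruits × 5 homes = 80. With 25% attrition, 80 × 0.75 = 60 = 12 × 5. These reproduce. The article gives no block length and no variance between periods, so both are assumed below.

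**3. Closed form for the arm dummy.** Let τ² be the between-resident variance within a home, s the share of it due to enrolment period, and N the residents analysed, split equally.

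- Variance reported without a block term: 4τ²/N.
- True variance with arms balanced within period: 4(1 − s)τ²/N.
- Ratio of standard errors: 1/√(1 − s). Most that can be recovered: 1 − √(1 − s).
- Coverage of a nominal 95% interval: 2Φ(1.96/√(1 − s)) − 1.

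| Assumed s | SE ratio | Most recoverable | Coverage |
|---|---|---|---|
| 5% | 1.026 | 2.5% | 95.6% |
| 10% | 1.054 | 5.1% | 96.1% |
| 20% | 1.118 | 10.6% | 97.2% |

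Example at 10%: 1.96 × 1.054 = 2.066, and 2Φ(2.066) − 1 = 0.961. Session-to-session noise enters both variances and pulls the ratio towards 1.

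**4. Simulation at the trial's size.** Resident-level analysis, 5 homes × 16, 2 or 4 time blocks per home, 25% attrition. The comparison is with a model adjusted for home only.

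| Assumed s | Fixed home-by-time terms: width without ÷ width with | Random block effect: interval narrower by |
|---|---|---|
| 5% | 0.97 to 1.00 | 2% to 3% |
| 10% | 0.98 to 1.01 | 3% to 5% |
| 20% | 1.03 to 1.05 | 6% to 9% |

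A ratio below 1 means that the fixed terms widen the interval. They add 10 − 5 = 5 or 20 − 5 = 15 parameters, and attrition leaves blocks incomplete. Without attrition the fixed-term ratios are 1.01 to 1.02, 1.03 to 1.04 and 1.06 to 1.09.

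The random effect kept coverage at about 94% to 96%. In the same set-up with s = 0 it still narrowed the interval by about 1% to 2%, because a variance estimate cannot fall below zero. Part of the gain shown at 5% is therefore not real.

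**5. Arm-by-phase contrast.** If efficacy is read as change from the resident's own baseline, and the period shift is the same in both phases, the shift cancels. With fixed block terms the simulated ratio was 0.94 to 1.00 for every s from 0 to 30%, so a block term brings no gain.

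**The case against.** A reader might infer that the interval is too wide as a matter of fact. The article does not support this: it gives no variance between periods, and if that variance is zero there is no excess width.

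A reader might also infer that the protocol itself expects period drift in the outcome, from the remark on six-month fluctuation in quality indicators. That remark supports individual over facility randomisation. The blocking rests only on unknown temporal effects. Where such drift reflects changing resident profiles, the level 2 covariates would absorb part of it.

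Nor does the closed form show that 5%, 10% or 20% of the completers are in effect thrown away. It is a ceiling, and fixed block terms do not reach it at this sample size.

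The strongest objection is the choice of contrast. This is a growth model with a baseline phase, and a shift common to both phases cancels in an arm-by-phase comparison. That stands, with two limits. The article writes out no such interaction and bases its power on the arm dummy. Equal shifts are also not assured: nursing home staff give mouth care at baseline and the research team gives it afterwards, so drift in a home's own care may touch the phases unequally.

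Finally, block terms are often settled in an analysis plan. But this article does list its model terms, and what it lists leaves out half of the blocking.

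**Conclusion.** The point holds as a minor, conservative matter of efficiency. The listed model carries one of the two blocking factors. For the listed arm dummy, if enrolment period explains 5% to 20% of between-resident variance (an assumption), about 2% to 10% of interval width is recoverable: 2% to 9% in simulation, against a closed-form ceiling of 10.6% at 20%. At the lower end the real gain is close to nil. For an arm-by-phase contrast with an equal shift in both phases there is no gain. There is no bias and no inflation of the type I error under any of these settings.

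The conclusion rests on time meaning study day and shift, which is likely but not certain, and on the assumed 2 or 4 time blocks per home.

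**What to change.** In the Statistical Analysis section, add the randomisation time block within nursing home as a random effect to both the CRB and the OHAT models. Do not enter it as fixed home-by-time terms. In the definition of time, state that it means study day and shift.

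The cost is a sentence or two, and the block should be available from the randomisation list. The downside is one more variance component, which may be estimated at or near zero; the model then reduces to the one already listed.

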### Recruitment, Sample, Sample Size

Power analyses were conducted in order to determine the sample size needed to provide sufficient power (1-β > .80) for assessing relationships between the explanatory variables and resistive behaviors and oral health outcomes. Data from the pilot study informed these analyses[35]. The power analyses were conducted using the software PINT[46], which is based on the work of Snijders and Bosker[47,48]. PINT estimates standard errors for regression coefficients in a two-level model, from which power can be calculated for a given effect size and significance level (α). Effect size was taken to be the absolute value of a standardized regression coefficient, and α was set at 0.05. Because PINT is designed for a two-level model rather than a three-level model, the second and third levels (participant and nursing home) were combined for power analysis purposes. Inputs into PINT include the total number participants to be sampled across all nursing homes (*N*) and the number of data collection times (*n*) per participant. Given *N *and *n*, the total sample size is *N *× *n*. Plausible effect sizes and other required inputs into PINT were based on the pilot study[35].

Based on results from the pilot study,[35] it is plausible to expect that the intervention group-control group dummy variable will have an effect size of 0.05 or larger in both the models for care resistive behaviors and the models for oral health outcomes. Power will then be high (1-β > 0.90) provided there are 42 observations per participant (twice daily for 21 days, so that *n *= 42), 12 participants across both the intervention and control groups within each nursing home (assuming 16 participants recruited, less 25% attrition), and five nursing homes (so that *N *= 12 × 5 = 60). This corresponds to a sample size of 2,520 (*N *× *n *= 42 × 60 = 2,520). If the effect size is somewhat larger (0.1), power is extremely high (1-β ≈ 1). In summary, given a 25% expected attrition rate, 80 participants should be recruited for the study (40 in intervention and 40 in control groups).

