### Treatment Fidelity

We will use several methods to monitor and enhance the reliability of our intervention[53]. Team members will be trained separately as either control interventionists and their CRB raters, or experimental interventionists and their CRB raters. Undergraduate and graduate nursing students will be hired and trained as experimental interventionists, control interventionists, or CRB raters. Training for the experimental interventionists consists of 3 hours of total training: best mouth care practices; explanation of dementia and theory behind threat-reduction techniques; detailed description of categories of CRB; strategies to recognize, prevent, and reduce CRB; and completion of specific instruments. The control interventionists receive 1 hour of didactic training regarding best mouth care practices and completion of specific instruments. The CRB raters receive 5 hours of training: 2 hours in the classroom and 3 hours in a NH. The first didactic hour addresses detailed descriptions of categories of CRB. The second didactic hour involves the correct use of the RTC-r and identifying type and quality of CRB from the training vide. The remaining 3 hours will occur in a NH during the baseline observations of mouth care and corresponding CRB data collection. The CRB raters will each complete one 3-hour period with either the PI or the project director (PD) during the 7-day observation period. At the conclusion of the 3-hour period, the CRB rater must have 90% agreement with either the PI or the PD; failure to reach 90% will result in retraining using the 2-hour didactic content and another 3-hour simultaneous data collection period until 90% is reached.

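### Interventionists and CRB raters each work in one arm only and the stated model has no staff term, so the arm effect's standard error is too small if staff differ, by an amount the protocol does not let one fix

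*Protocol article*

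**What the plan says.** All references are to the protocol article.

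- **Pairing.** Randomization and Control of Cross-Contamination: "CRB raters will be paired exclusively with their control interventionists or with their experimental interventionists, to avoid bias in rating".
- **Training.** The same section says that "Training for CRB raters, control interventionists, and experimental interventionists will occur separately", with no cross-training. Treatment Fidelity groups raters with their arm: "Team members will be trained separately as either control interventionists and their CRB raters, or experimental interventionists and their CRB raters". Student nurses are hired for one role; their number is not given.
- **Rater certification.** Treatment Fidelity describes one 5-hour programme for raters. It requires 90% agreement with the principal investigator (PI) or the PD during the baseline week, with retraining until this is met.
- **Baseline week.** Methods/Design has the raters, as a group, observe residents of both arms while nursing home staff give the care.
- **Model.** Under Statistical Analysis the first level is the date/time of observation, "the second level is the participant; and the third level is the NH in which the participant resides". The listed covariates are dosage, frequency, time, phase, arm and resident characteristics. No staff variable appears.
- **Oral health.** Instruments and Measures has the OHAT scored by separate assessors blinded to assignment.

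**The concern.** The CRB outcome is a count of behaviours made by a person in the room, divided by session length. If every rater and every interventionist sits in one arm, what is particular to them is shared by many residents of that arm and by none of the other. The participant effect does not capture this, because it treats residents of the same arm as independent. The nursing home effect does not either, because each home contains both arms. More sessions per resident do not shrink it.

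Two separate things follow:

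1. **Random variation between staff** enters the difference between arms but not its modelled standard error, so the test of H1 rejects too often.
2. **A systematic difference between the two rater groups** that arises or grows after the baseline week looks exactly like a treatment effect. Pairing is offered as a protection against rating bias, but it leaves this form of bias impossible to estimate.

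**Working it through.** **The plan's own figures.** 60/(1 − 0.25) = 80 and 60 × 42 = 2,520 reproduce ("This corresponds to a sample size of 2,520"). With "α was set at 0.05", taken as two-sided, and all 2,520 observations independent, SE = √(1/2,520) = 0.0199. At a coefficient of 0.05, power = Φ(0.05/0.0199 − 1.96) = 0.71; at 0.1 it is 0.999. The printed claim, "Power will then be high (1-β > 0.90) provided there are 42 observations per participant", therefore does not follow from the printed inputs alone. The variance inputs to PINT are not printed, so I leave that open. What matters here is that the inputs described are participants and occasions, with no staff clustering.

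**Hand calculation.** From the document: 30 completers per arm (60/2) and 30 × 42 = 1,260 sessions per arm. Assumed: resident variance 0.3, session variance 0.7, staff variance 0.05 (about a 5% share), 5 staff per arm.

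- Variance of the arm difference from residents and sessions: 2 × (0.3/30 + 0.7/1,260) = 0.0211.
- Added by staff: 2 × 0.05/5 = 0.0200. True total: 0.0411.
- If staff rotate within the arm, the model sees about 0.0211. SE ratio = √(0.0411/0.0211) = 1.40; type I error = 2 × (1 − Φ(1.96/1.40)) = 0.16.
- If each resident keeps one staff member, staff variance is absorbed in the resident term and the model sees 2 × (0.35/30 + 0.7/1,260) = 0.0244. SE ratio = √(0.0411/0.0244) = 1.30; type I error = 0.13.

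**Simulation under no effect.** 20,000 runs per cell; 5 homes, 30 residents per arm, 42 sessions; resident variance 0.3, home variance 0.05, total variance 1; home and resident accounted for, staff ignored. Entries are type I error in %, with staff fixed to residents / staff rotating.

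| Staff share of variance | 2 staff per arm | 4 | 6 | 10 |
|---|---|---|---|---|
| 1% | 10.2 / 10.6 | 7.4 / 7.8 | 6.6 / 6.6 | 5.5 / 6.0 |
| 5% | 26.0 / 27.4 | 16.0 / 18.1 | 11.3 / 13.9 | 8.4 / 10.2 |
| 10% | 36.9 / 40.4 | 23.0 / 28.0 | 15.9 / 21.7 | 10.8 / 16.1 |

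With zero staff variance the rate is 4.7 to 5.2%, so the excess comes from the staff term alone.

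**Sensitivity to the definition of share.** If the staff share ρ is instead the correlation between residents' means, the variance inflation is 1 + (30/K − 1)ρ for K staff per arm. With K = 5 this gives a type I error of 5.6% (ρ = 0.01), 8.0% (0.05) and 11.0% (0.10); with K = 2 it gives 6.6%, 13.3% and 20.6%.

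**Systematic rating difference.** A hypothetical difference of 0.1 SD between the two rater groups, times the 0.5 SD of a balanced arm dummy, is a standardised coefficient of 0.05. That is the lower end of what is planned for: the arm dummy "will have an effect size of 0.05 or larger in both the models for care resistive behaviors and the models for oral health outcomes".

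**The case against.** The strongest reply is that rater differences are already controlled. Raters of both arms follow one described programme and are certified against the PI or PD to the same pass mark. That stands as a real safeguard, and the two accounts of who is trained with whom do not show that calibration differs by arm. But certification takes place in the baseline week, no repeat during the 21 intervention days is described, and it does nothing about differences between interventionists.

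A reader might infer that rater threshold is completely confounded with treatment. The documents do not support that. Raters as a group see both arms at baseline; if each of them does, a stable difference in threshold can be estimated from that week, and only a later difference or drift is aliased with arm. Whether each rater sees both arms is not stated, and the model has no rater term to use the information.

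A reader might also infer that staff are few and the inflation therefore large. No number is given, and with 10 staff per arm and a 1% share the rate is close to nominal.

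Pairing has a purpose too: a rater who alternates between two styles of care could work out the arm and score accordingly, which no random effect corrects. That objection stands against crossing raters in the intervention phase. Confining interventionists to one arm likewise serves contamination control and need not change.

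Lastly, an analysis plan not shown here could add a staff random effect. It could not undo the pairing, and the article sets out its model's levels and covariates without one.

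**Conclusion.** The point holds in limited form. Staff are nested in arm, and the model as stated omits them. The direction is certain if staff variance is above zero, which is very likely. The size is not: about 5.5% to 40% over the assumed ranges, and about 13 to 16% in the middle case of 5 staff per arm and a 5% share. No one of these figures can be presented as this trial's error rate.

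A systematic rating difference arising after baseline cannot be separated from treatment under the pairing, and certification only reduces that risk. The rater part concerns CRB only, because the OHAT has separate blinded assessors; the interventionist part can reach both outcomes. The 0.05 coefficient is a floor for the planned effect, so a 0.1 SD rating difference should not be described as equal to the whole of it.

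**What to change.** 1. **Model.** Add a random effect for interventionist to the CRB and OHAT models and one for rater to the CRB model. Test the arm effect with small-sample degrees of freedom based on staff numbers, about 2K − 2 (8 with 5 staff per arm). If each rater works with a single interventionist, the two effects cannot be separated and one pair effect should be fitted. These terms deal with random staff variation only, so step 2 is also needed.
2. **Check on rating.** Keep the pairing. Have the PD score the RTC-r beside the rater at the 10% of sessions already observed in each arm, and report rater-minus-PD differences by arm. On the planned 2,520 sessions that is about 252, or 126 per arm.
3. **Baseline week.** State that each rater observes residents of both arms.

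The cost is wider confidence intervals, some extra scoring by the PD and a line in the rater rota; no extra staff. The PD knows the arm, so step 2 checks for differential rating but is not a blinded reference. Crossing raters over arms in the intervention phase is not required, since it risks unblinding them.
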